## Abstract

**Background:**

The incidence of chronic diseases associated with physical inactivity is on the rise, being one of the leading risk-increasing factors for early death rates throughout the world. Often, physical activity interventions fail to deliver sustained adherence over time due to limiting tailoring to individual baseline characteristics, leaving out contextual changes over time. One solution for this issue may be the use of adaptive interventions relying on contextual multiarmed bandits, a type of reinforcement learning algorithm, that can use baseline and contextual individual data to personalize aspects of the intervention, such as developing personalized workout plans.

**Objective:**

The main objectives of this study are (1) to determine the effectiveness of contextual bandits for automated goal setting in the context of a web-based physical activity intervention, (2) to understand the role of user characteristics impacting ideal workout schedules based on adherence to predetermined goals, and (3) to explore the influence of user autonomy on recommendation effectiveness.

**Methods:**

We developed a protocol for a web-based adaptive intervention trial to investigate the effectiveness of goal recommendation (task difficulty) based on reinforcement learning. The web application (named Apptivate) creates workout routines with 3 different difficulty levels, changing the total workout duration as well as rest times between exercises. Physical activity professionals validated the routine design, ensuring that workouts match recommended guidelines for healthy adults. An initial pilot was conducted, aiming for 800 university students to test the web application for 1 week, to provide initial data to calibrate the algorithm as well as overall feedback for the web application. For the main study, a total of 500 university students will be recruited to participate for 40 days during early 2026. Participants will be divided into 3 groups: user choice (no recommendation), user choice with automated recommendations (contextual bandits), and automated plans without choice.

**Results:**

The pilot was conducted in September 2025. Data analysis for the pilot is undergoing, and the main study is planned for early 2026. Our main statistical analysis includes a direct comparison (paired tests) between success rates across intervention arms, as well as by difficulty level and individual characteristics.

**Conclusions:**

Physical activity maintenance is key to achieving long term health goals. Tailored digital interventions are promising strategies for physical activity adherence, but personalization often fails to consider dynamic contextual changes. The proposed protocol for a physical activity intervention using adaptive experimentation can provide robust causal inference on the role of choice versus autonomy when goal difficulty is tailored under an adaptive data-driven approach.

**International Registered Report Identifier (IRRID):**

PRR1-10.2196/73766

## Introduction

Regular physical activity (PA) is essential for maintaining overall health and well-being [1]. Extensive research has demonstrated that consistent exercise is associated with numerous health benefits, including improved sleep quality, enhanced mood, and a reduced risk of noncommunicable chronic diseases such as diabetes, stroke, depression, and dementia. In contrast, physical inactivity has been identified as one of the leading risk factors for premature mortality and a significant contributor to the rising health care costs [2-4]. Despite the well-documented benefits of PA and risks associated with a sedentary lifestyle, 31% of the global adult population—equivalent to 1.8 billion adults—fail to meet the recommended levels of PA [5]. Even with unwavering global efforts from national and international policy, mass media campaigns, and social support and educational programs [6], the number of adults who are physically inactive has been steadily increasing in high-income countries [7].

To address this public health issue, researchers have designed and implemented various interventions aimed at promoting regular exercise adherence, many of which are based on prominent social and psychological theories [8,9], such as theory of planned behavior [10] or self-determination theory [11]. Although these interventions have shown promise in increasing individuals’ intentions to engage in PA, a key challenge lies in translating these intentions into sustained behavior [12,13]. This discrepancy is known as the “intention-behavior gap,” emphasizing that goal intentions only partially materialize on corresponding actions [14]. Studies indicate that individual factors such as lack of motivation and low self-efficacy, as well as environmental barriers, such as time constraints, can hinder individuals from acting on their intentions, even when they recognize the benefits of PA [13,15]. Moreover, these factors are highly heterogeneous across individuals and time. Thus, addressing these challenges requires individualized, flexible, and engaging interventions that consider individual needs, preferences, and contexts, and that promote self-efficacy and focus on closing the intention-behavior gap.

Mobile apps have emerged as promising platforms for delivering effective health interventions owing to widespread technological access and potential for personalization or tailoring [16]. While the overall evidence on the effectiveness of app-based mobile health (mHealth) interventions on PA engagement is mixed [17-19], interventions that allow for tailoring (ie, fitting interventions to users), especially considering changes in context over time, show promising results [16]. For example, a study in 2006 demonstrated that computer-tailored interventions, which provide personalized feedback and actionable recommendations, significantly increased PA levels among participants compared to generic advice [20]. Similarly, researchers in 2011 found that interventions incorporating goal-setting, self-monitoring, and personalized planning were more effective in promoting sustained behavior change [21]. These approaches recognize that a “one-size-fits-all” strategy is often insufficient, as individuals face unique challenges such as time constraints, lack of social support, or low self-efficacy. By addressing these barriers through tailored solutions, such as adaptive goal-setting, context-specific reminders, or individualized support systems, interventions can better align with participants’ lifestyles and may potentially enhance their ability to act on their intentions [22,23].

The taxonomy of personalization features is extensive, as apps allow for data-driven mechanisms that can respond to user behavior and real-time context, delivering messages, adapting to user experience, tailoring interactions with other participants, and providing user targeting, among other features [23]. However, in most apps, personalization is designed to increase user engagement with the app rather than focusing on sustained behavior adoption [24], which may be a consequence of lacking integration between app-based health research and existing theoretical frameworks explaining behavior adoption [25]. Evidence from such behavioral models, such as the integrated behavior change (IBC) model [26,27], propose that behavior adoption requires sustained effort, that is, a sustained focus on realizing behavior change goals (ie, plans) over time (Figure 1). Therefore, one way to potentially enhance the effectiveness of tailoring in app-based interventions is to focus on such goals, with personalized goals that are selected to fit individuals’ unique profile (eg, adapting difficulty to individuals’ preferences or characteristics) in order to maximize the likelihood of goal completion over time. Such personalization should acknowledge time-variant factors (or contexts) that can affect individuals on a daily basis, as well as time-invariant aspects that could vary dramatically across users. Earlier work on message tailoring has suggested that including elements of multiple dominant psychological theories into tailoring approaches increases overall effectiveness [28], suggesting the IBC model, which integrates across the major dominant psychological theories [26,27], is well-suited for developing tailoring approaches.

**Figure 1 figure1:**
[figure not shown]
Integrated behavioral change model (source: Hagger and Chatzisarantis [26]).

With technological advances in artificial intelligence, personalization has become easier to implement in dynamic settings, where users are interacting repeatedly with tailored components. In particular, contextual multiarmed bandits, or simply contextual bandits (CBs), have become an effective reinforcement (machine) learning personalization tool in the health behavior domain, where treatment (option) recommendations are optimally determined to maximize user performance using individual characteristics and behavior [29]. In short, CB algorithms use all available data to predict the action that would provide the best outcome to a given user, while learning from the relative performance of all possible actions. In experimental literature, there is a novel approach using CBs named adaptive interventions, emphasizing the idea that we can pose a sequential field experiment with an adaptive sampling procedure that aims to determine which types of individuals benefit from certain intervention arms over time, while also learning about the average effectiveness of each arm [30,31]. Adaptive interventions allow us to estimate the relative effectiveness of each arm while providing the optimal path for each user, based on their expected behavioral response. Overall, CBs have important advantages as an automated personalization tool, requiring less data to determine which interventions are more effective overall and allowing an understanding of which characteristics are most likely to influence individuals’ performance.

Adaptive interventions using CB algorithms have become popular in the public health domain, with promising results [16,23,32]. Systematic reviews for adaptive interventions targeting PA and sedentary behavior reveal that most studies focus on tailored feedback as the main personalization component, with few interventions focusing on goal tailoring. Moreover, studies designed with goal setting features mostly focus on difficulty progression over time (eg, increasing duration or reducing resting time) or alternating types of exercises (eg, cardio, strength, and flexibility) based on the user’s health profile [23]. In particular, while difficulty progression seems reasonable as mastery increases, evidence on motivation shows that dynamic environmental factors can strongly influence goal completion as difficulty increases [33]. Altogether, to date, it is still unclear to what extent automated personalized goal difficulty recommendations over time and individual preferences influence health behavior adoption.

While machine learning approaches such as CBs offer promise by matching individuals based on their characteristics or context, this optimal recommendation could be seen as a directed action (data-driven), or a recommendation, mediated through individual choice. This is particularly relevant in the context of exercise, where preferences for workout intensity and capabilities to do more demanding exercises can differ widely between individuals [34]. Enabling respondents to choose their workouts, rather than be assigned one through machine learning, respects these diverse preferences and could enhance intervention effectiveness. That is, according to self-determination theory, an influential psychological theory of motivation, being able to choose enhances autonomy, a key driver of intrinsic motivation [35]. Furthermore, evidence suggests that individuals may benefit from a process of self-experimentation to find what works best for them [36]. A meta-analysis shows the potential of choice-based interventions in the context of health behaviours (including exercise), showing improved adherence and reduced dropout across various health behaviors [37]. Past research has found that providing individuals with choice in PA positively influences their perception of exercise [38,39], general well-being [40], as well as adherence to the intervention regime [41]. However, enabling choice is not without risks; individuals may opt for interventions that are ineffective for them due to, for instance, misjudging their own self-control [42] or selecting appealing but ultimately ineffective strategies [43]. Thus, in the context of machine learning–based tailoring, incorporating a “choice” arm allows for the investigation of how algorithmically assigned interventions compare with those selected by individuals themselves, enabling a direct comparison between data-driven assignment of exercise goals versus self-chosen goals.

This study explores three research questions to evaluate the effectiveness of adaptive interventions that focus on goal difficulty and user choice:

Can CBs outperform performance success rate (goal completion) relative to user-chosen workouts?Which user characteristics are most relevant for determining choice probabilities among intervention arms?To what extent does user autonomy in choosing a workout plan influence the effectiveness of recommendations based on CBs?

By addressing these questions, this experiment aims to contribute to the growing body of research on adaptive behavior change interventions. Understanding the interplay between user choice and data-driven recommendations can inform the development of more effective mHealth apps [44].

## Methods

### Apptivate

For this project, the experiment will be conducted using the web application “Apptivate” [45], extending its initial functionally to incorporate CB algorithms connected to a routine difficulty assignment. Apptivate creates workout routines with 3 different difficulty levels, changing the total workout duration as well as rest times between exercises. PA professionals validated the routine design, ensuring that workouts match recommended guidelines for healthy adults. The overall design allows users to conduct exercises without equipment following the in-app instructions, covering different muscle groups as well as providing both warm-up and stretching exercises.

Apptivate adopts the IBC model for PA [26] as a framework for tailoring workout difficulty recommendations (ie, goals). By leveraging the IBC model, the app ensures that its recommendations address not only dynamic changes in behavior over time but also the psychological factors that influence behavior change. In particular, we capture data on the psychological constructs defined in the IBC model, which are later used as contexts for the algorithm learning process. Participants that take part in the main study will be assigned to 1 of 3 conditions:

Choice-driven: Users select their desired workout difficulty level from a predefined menu. This approach provides users with a sense of autonomy and control over their exercise routine. Choice-driven tailoring leaves the selection of the intervention to the user, allowing individuals to reveal their preferences in a participatory process [33].Data-recommended: The CB algorithm determines optimal workout difficulty (based on user data and the IBC model) and provides a recommendation to the user, but the user retains the option to choose an alternative. This design allows us to investigate the interplay between user autonomy and the effectiveness of data-driven recommendations [27].Data-driven: The CB algorithm automatically recommends workouts based on user data, including contextual features based on the IBC model, without any opportunity to opt into a different difficulty level. This method leverages a machine learning approach to personalize workout plans and potentially optimize user performance (measured as goal completion).

Apptivate also includes several personalization features to enhance user engagement [15,23]. Users can change their username and avatar, as well as opt for timed notifications. The system includes motivational messages, a progress tracker, and routine feedback (Figure 2).

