### Contextual Bandits Algorithm

The contextual multiarmed bandit model used in this study is a type of reinforcement machine learning approach, which uses experimentation to learn about users’ performance and recommend the best potential option. As shown in Figure 3, the algorithm incorporates users’ past outcomes (target) and context (features) to assign probabilities to each treatment option and recommend the best possible treatment in the future (higher likelihood of success, noted in green). Once given a recommendation, users respond (either positively or negatively in this case), and this information is used for further training the algorithm for the next interaction. There are several algorithms developed to solve CB models, differing in how probabilities for each option are updated (learning) and the degree of exploration (randomness) involved in providing users with different options.

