To train the reinforcement learning algorithm for the study, initial data are required for which a pilot stage was designed. In this stage, 800 participants will be recruited at one university in order to provide 1 week of activity using the app (two 3-day rounds with a rest day in between). In order to determine the sample size for the pilot, standard power calculation was assumed with a uniform distribution over 3 arms (standard randomized controlled trial). With 665 observations, the pilot is sufficient to detect differences between users. The data from round 1 will be used to estimate the optimal arm for round 2, which will be used for calibration. Participants complete a comprehensive baseline survey eliciting the IBC model as well as several other relevant characteristics (eg, time and risk preferences; see Multimedia Appendix 1) and then are assigned randomly between the 3 difficulty levels for the first round. After completion, participants are compensated for their time. Individuals can opt out from the study at any time.

During the main part of the study, 500 participants will be recruited from multiple sites expecting to participate in a medium-term challenge, completing 10 rounds, equivalent to 39 consecutive days using the app (including rest days). As noted earlier, this provides 5000 unique examples for the algorithm to determine optimal policy over time. Users will be allocated to each arm based on their baseline survey and the trained algorithm during the pilot stage. Regardless of their initial difficulty assignment, each participant will be randomly allocated with equal probability between (1) choice-driven, (2) data-recommended, and (3) data-driven arms. Participants will be compensated for their time, and there will be additional prizes using a lottery mechanism that favors (in probability) those users completing more consecutive workout routines over the course of the study. In both the pilot and main experiment, participants will stay engaged via direct email, push notifications, and social media campaigns.

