### Data Collection

Data collection in this study spans multiple dimensions, capturing individual characteristics, app usage patterns, and most importantly, user performance. This multifaceted approach allows us to provide insights on the potential heterogeneous impact of tailored goal-setting interventions.

Baseline survey: Participants will complete an online survey to gather demographic information (eg, age, gender, and socioeconomic status), fitness history (eg, frequency and type of PA), and constructs from the IBC model, such as perceived behavioral control, motivation types (autonomous and controlled), and self-regulatory capacities.Fitness app data: The app will track participant engagement and outcomes, including goal completion rates, total time spent on physical activities, and engagement metrics (eg, frequency of app interactions).Algorithm data: The CB algorithm embedded in the app will collect data on contextual features (eg, user preferences, past performance, and fitness level) and reward functions to predict optimal goals and adapt recommendations over time.

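### Goal completion is both what the algorithm maximises and how RQ1 judges it, so higher completion alone would not show more physical activity

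*Protocol article*

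**What the plan says.** The Introduction poses research question 1 as: "Can CBs outperform performance success rate (goal completion) relative to user-chosen workouts". The algorithm is described as pursuing the same quantity in three places:

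- The Introduction says goals are personalised "in order to maximize the likelihood of goal completion over time".
- The Apptivate section says of the data-driven arm: "This method leverages a machine learning approach to personalize workout plans and potentially optimize user performance (measured as goal completion").
- The Contextual Bandits Algorithm section says the algorithm is to "recommend the best possible treatment in the future (higher likelihood of success, noted in green").

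What the algorithm sets is the difficulty level: "Apptivate creates workout routines with 3 different difficulty levels, changing the total workout duration as well as rest times between exercises". The user sets it in the choice-driven arm. The algorithm sets it without opt-out in the data-driven arm. In the data-recommended arm the algorithm proposes and the user may override.

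Data Collection lists as tracked "goal completion rates, total time spent on physical activities, and engagement metrics". The Statistical Analysis section names completion, engagement and satisfaction for the comparison of the three groups; activity time is not named. The Results section adds a comparison of success rates by difficulty level. Hypothesis 1 in Study Design is that personalisation with bandits narrows the intention-behaviour gap for some users, and the Discussion presents the approach as a way to promote sustained activity.

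**The concern.** A completed workout need not be the same amount of exercise in each arm, because the arms differ in who sets the size of the goal. An algorithm rewarded for completion has a direct route to a higher score: set smaller goals. Nothing in the text weights the reward by difficulty or duration, or limits how far the assignment may drift to one level.

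What is at stake is the reading of the main result. RQ1 could be answered yes because goals were lowered, while participants in the algorithm arm exercised no more, or less, than those who chose for themselves. Hypothesis 1 and the Discussion invite a reading in terms of behaviour, which completion alone would not carry.

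**Working it through.** **Figures in the plan.** The protocol gives no completion rate, workout duration or choice mix by level, and no effect size, so there is no stated figure on this point to reproduce. It gives 500 participants, 10 rounds (500 × 10 = 5000 examples, as stated) and equal allocation (500 / 3 ≈ 167 per arm).

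**Assumed inputs.** Durations are 15, 25 and 35 min for easy, medium and hard. Completion by level and choice mix vary as shown. Completion does not depend on who set the level, so personalisation brings no benefit.

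**Formulas.** With level shares w, completion p and duration d:

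- completion = Σ w·p
- completed minutes per session = Σ w·p·d

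**By hand, 80/65/50% completion.**

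- Even mix: (0.80 + 0.65 + 0.50) / 3 = 0.65, and (12 + 16.25 + 17.5) / 3 = 15.25 min.
- All easy: 0.80, and 0.80 × 15 = 12 min.
- Difference: +15 points, and 12 / 15.25 − 1 = −21% in minutes.

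**With 10% random exploration** (the best level gets 0.9 + 0.1/3 = 0.933, the others 0.033 each):

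| Completion easy/medium/hard | Choice mix | Choice arm | Algorithm arm | Difference |
|---|---|---|---|---|
| 80/65/50 | even | 65.0%, 15.25 min | 78.5%, 12.3 min | +13.5 points, −2.9 min |
| 80/65/50 | 60/30/10 | 72.5%, 13.8 min | 78.5%, 12.3 min | +6.0 points, −1.5 min |
| 70/65/60 | even | 65.0%, 15.9 min | 69.5%, 11.0 min | +4.5 points, −4.9 min |
| 70/65/60 | 60/30/10 | 67.5%, 13.3 min | 69.5%, 11.0 min | +2.0 points, −2.2 min |
| 65/65/65 | any | 65.0% | 65.0% | 0 points |
| 60/65/70 | even | 65.0%, 16.6 min | 69.5%, 23.7 min | +4.5 points, +7.1 min |

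Minutes are left out of the flat row because on a tie the algorithm has no reason to prefer any level.

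**Simulation.** There were 1000 runs per setting, with 167 users per arm, 10 rounds, an epsilon-greedy policy (epsilon 0.1) and a random user intercept with SD 1 on the logit scale. The algorithm arm had significantly higher completion (z > 1.96) in:

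- 99.9% of runs for 80/65/50 with even choice (11.9 v 14.9 completed min; about 91% of its sessions at the easy level);
- 52% for 80/65/50 with 60/30/10 choice (11.9 v 13.3 min);
- 22% and 7% for 70/65/60 with even and 60/30/10 choice (11.6 v 15.4 and 11.6 v 12.7 min);
- about 2% for flat completion, close to the nominal one-sided rate.

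Where completion falls with difficulty, these are real differences in completion, but they come entirely from the level mix.

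**When minutes do not fall.** Easy workouts yield as many completed minutes as hard ones if p(easy) / p(hard) reaches 35 / 15 = 2.33. At 80/65/50 the ratio is 1.6. A steep enough gradient would therefore raise both completion and minutes.

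**The case against.** The strongest reply is that the trial answers the question it asks. Participants are randomised with equal probability, so comparing completion under three ways of setting difficulty is a valid randomised contrast. The level mix is how the intervention works, not a confounder, and RQ1 does not ask who exercises longer. This stands. A reader might infer that completion is biased or not comparable between arms; the documents do not support that. The difficulty lies in moving from completion to behaviour.

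A reader might also infer that the algorithm will settle on easy workouts and produce a hollow win. The documents do not show this either. No gradient is given, and the implemented reward is not fully specified: it is defined formally only as lying between 0 and 1. The text describes it as completion, but a weighting could appear in the full protocol.

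The lottery, which offers "additional prizes using a lottery mechanism that favors (in probability) those users completing more consecutive workout routines", might be thought to make matters worse. If anything it would lead choosers towards easier levels and narrow the gap, and the text does not say how the odds relate to level. It forms no part of this point.

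There are partial safeguards. Activity time is tracked, success is also examined by difficulty level, and professionals validated the routines against guidelines. The by-level split could reveal a shift in mix, but level is set after randomisation, so within-level contrasts are not randomised comparisons. Validation limits how light a routine can be; it does not make the levels equal goals.

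Finally, minutes also depend on level and favour whichever arm assigns longer workouts. Minutes should therefore not replace completion, and a mandatory co-primary is not required. The two outcomes need to be read together.

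**Conclusion.** The point holds as one of interpretation. As described, the algorithm's target and RQ1's yardstick are the same quantity, its only lever is the size of the goal, and no activity outcome is named in the arm comparison. Higher completion can therefore coincide with equal or less activity, and completion alone does not support a claim about the intention-behaviour gap or sustained activity.

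The size cannot be known from the document. It is nil with a flat gradient. With a reverse gradient both completion and minutes rise. It is about +4.5 points at 70/65/60% with an even choice mix, and about +15 points with 21% fewer completed minutes at 80/65/50% (all easy against an even mix). It shrinks if choosers also favour easy workouts. All of this rests on assumed completion rates, durations and choice mixes. Pilot round 1 randomised users across the three levels, so its data can show whether completion falls with difficulty before the main study begins. No view is taken on which level suits whom.

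**What to change.** In the Statistical Analysis section:

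1. Add activity time per participant, taken from the total activity time the app already tracks, as a prespecified key between-arm outcome analysed by randomised arm.
2. State that contextual bandits will be said to improve physical activity behaviour only if completion is higher and activity time is not lower, and fix in advance how not lower will be judged. Otherwise report the result only as higher completion of the goals set.
3. Report the level mix by arm beside each completion contrast.
4. Label comparisons by difficulty level as descriptive, because level is set after randomisation.

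Before the main study, report completion by level from pilot round 1.

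The cost is a change of wording, one more outcome to analyse and a somewhat stricter claim. No new data are needed. The tracked quantity is total time rather than completed-workout time, so the outcome should be defined on what the app records.
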